## Abstract

**Introduction:**

Glycemic variability (GV) represents the amplitude of oscillations in glucose levels over time and is associated with higher mortality in critically ill patients. Our aim is to evaluate the impact of GV on acute ischemic stroke (IS) outcomes in humans and explore the impact of two different insulin administration routes on GV in an animal model.

**Methods:**

This translational study consists of two studies conducted in parallel: The first study is an observational, multicenter, prospective clinical study in which 340 patients with acute IS will be subcutaneously implanted a sensor to continuously monitor blood glucose levels for 96 h. The second study is a basic experimental study using an animal model (rats) with permanent occlusion of the middle cerebral artery and induced hyperglycemia (through an intraperitoneal injection of nicotinamide and streptozotocin). The animal study will include the following 6 groups (10 animals per group): sham; hyperglycemia without IS; IS without hyperglycemia; IS and hyperglycemia without treatment; IS and hyperglycemia and intravenous insulin; and IS and hyperglycemia and subcutaneous insulin. The endpoint for the first study is mortality at 3 months, while the endpoints for the animal model study are GV, functional recovery and biomarkers.

**Discussion:**

The GLIAS-III study will be the first translational approach analyzing the prognostic influence of GV, evaluated by the use of subcutaneous glucose monitors, in acute stroke.

*Trial registration*
https://www.clinicaltrials.gov (NCT04001049)

## Methods

The translational study consists of a multicenter observational study that will include patients with acute IS and a parallel basic experimental study using an animal model.

### Design

#### Clinical study

Observational, multicenter, prospective study.

##### Patient population

The inclusion and exclusion criteria are listed in Table 1.

**Table 1 Tab1:** GLIAS-III main inclusion and exclusion criteria

Inclusion criteria	Exclusion criteria
Male and female patients older than 18 years, with acute IS Inclusion in the study within the first 24 h of stroke onset A prestroke score on the Modified Rankin Scale (mRS) ≤ 1 Signed informed consent	Transient ischemic attack Predicted need for an MRI within the first 96 h after inclusion A health status, clinical condition or other characteristic that precludes appropriate diagnosis, treatment, or follow-up in the trial Current drug or alcohol use dependence Participation in a therapeutic clinical trial

##### Randomization

None (observational study).

##### Intervention

After the participants sign the informed consent form, they will be implanted a CGM subcutaneously to monitor glucose levels for 96 h. These devices are of common use in the management of type 1 diabetes and they have been proven to be safe in stroke patients when used in research studies. Capillary finger prick glucose levels will be recorded every 4–6 h according to the standard protocols of each center, as well as the insulin administration characteristics (type, dose and route of administration) as per the treating physician’s criteria, following the local protocols for the in-hospital management of hyperglycemia. The treating physician and the nursing personnel will be blinded to the readings taken by the CMG device. All study centers will use the same brand of CGM (CE-marked). All patients will be managed according to current guidelines for acute stroke management and local protocols, including treatment with intravenous thrombolysis or mechanical thrombectomy if applicable. No laboratory data other than HbA1c will be collected for the study proposal. Any emergent laboratory abnormality during the study follow-up will be recorded as a complication.

##### Study schedule

The study will last 3 months per patient according to the schedule shown in Table 2.

**Table 2 Tab2:** GLIAS-III flow diagram

	Baseline	96 h (± 6 h)	Day 7 or discharge (± 1 d)	Day 30 (± 2 d)		Day 90 (± 3 d)	
Signed informed consent	X						
Inclusion/exclusion criteria review	X						
Past medical/surgical history	x						
Pre-stroke treatments	x						
Modified rankin scale	(Pre-stroke)		X	X		X	
NIHSS	X	X	X	X		X	
Reperfusion treatment received	X						
HbA1c	X					X	
Continuous blood glucose monitoring	< –––––––––––––– >						
Capillary glucose levels (per local protocols)	< –––––––––––––– >						
Insulin (type, dosage and route) administered according to local protocols	< –––––––––––––– >						
Systemic and neurological complications	< ––––––––––––––––––––––––––––––––––––––––– >						
Stroke etiological subtype			X				
Secondary stroke prevention treatments			X		X		X

*HbA1c* glycated hemoglobin, *NIHSS*, National Institutes of Health Stroke Scale

##### Primary endpoints

GV. Defined as the standard deviation of the mean blood glucose level for each patient [17]. For the main analysis, we will use the GV value recorded within the first 48 h after stroke onset. We will conduct an exploratory analysis to evaluate the GV between 48 and 96 h.Mortality: in-hospital and at 3 months.

##### Secondary endpoints

Modified Rankin Scale (mRS) and National Institutes of Health Stroke Scale. (NIHSS) at 3 months. These scales will be evaluated by a neurologist blinded to the GV values.Other GV measurements: coefficient of variation (CV), mean amplitude of glycemic excursions (MAGE); mean absolute glucose (MAG) rate of change [2, 17, 18]. CV is less influenced by mean glucose and is a good marker of hypoglycemia. A threshold value to define low and high GV using CV has recently been proposed [19]. MAGE and MAG are indexes used for studying glycemic variability in clinical trials, and normal references values for people without diabetes using CGM are available [18]. On the other hand, MAGE can provide information about the influence of the largest glycemic excursions.Neurological or systemic complications during follow-up. The following complications are pre-specified by protocol and will be checked at each visit: coma, seizures, early neurological impairment, brain edema, hemorrhagic transformation, recurrent strokes, acute coronary syndrome, pulmonary thromboembolism, respiratory infection, urinary infection, sepsis. Any other non-pre-specified complication reported during follow-up will be also recorded.

##### Data collection and management

In addition to the primary and secondary endpoints, the following data will be collected:Demographic data and risk factors: age, sex, race, weight, height, diabetes, hypertension, dyslipidemia, coronary arterial disease, atrial fibrillation, metabolic syndrome, chronic renal disease (eGFR of less than 60 ml/min/1.73m2), tobacco use and alcohol abuse.Pre-stroke pharmacological treatments: antiplatelets, anticoagulants, blood-pressure lowering drugs, antidiabetics and hypolipemiants.Stroke data: stroke severity on admission (NIHSS), date of stroke onset (or last time known asymptomatic in those patients with unknown stroke onset), stroke etiological subtype, treatment with intravenous thrombolysis or mechanical thrombectomy.Vital signs at baseline visit: body temperature, blood pressure, heart rate, respiratory rate.

Data will be prospectively included in a study-specific web-based database developed and managed by the Clinical Trials Unit at Hospital 12 de Octubre which belongs to the Spanish Clinical Research Network (SCReN), independent form the study sponsor. All data management will follow the principles of the European regulations for biomedical research ensuring confidentiality. In compliance with European regulations/International Conference of Harmonization Good Clinical Practice Guidelines, the investigator and the institution are required to permit direct access to authorized representatives of the Ethics Committee to review the subject’s original medical records for verification of study-related procedures and data.

##### Data monitoring body

Monitoring will be conducted by dedicated personnel at La Paz University Hospital. All data management will follow the principles of the European regulations for biomedical research, ensuring the confidentiality of all personal data. In compliance with European regulations/International Conference of Harmonization Good Clinical Practice (ICHGCP) Guidelines, the investigator and institution are required to permit authorized representatives of the regulatory agency(s), and the IEC/IRB direct access to review the subject’s original medical records for verification of study-related procedures and data.

##### Sample size estimates

Based on the data from the GLIAS-II study, [11] conducted in a similar setting and using nQuery Advisor software (Statistical Solutions Ltd., Cork, Ireland), we calculated that a sample of 340 patients will be required to achieve 80% statistical power and a confidence level alpha of 0.05 to detect a significant effect of GV on mortality at 3 months.

#### Experimental animal model of stroke and hyperglycemia in rats

The basic experimental study will use an animal model of permanent middle cerebral artery occlusion (MCAO) and hyperglycemia in rats. The experiments are designed to minimize animal suffering in compliance with our Ethical Committee for the Care and Use of Animals in Research (EU directives 86/609/CEE and 2003/65/CE).

##### Study groups

A total of 60 Sprague–Dawley rats (8–9 weeks old, weighing 200–250 g) will be randomly assigned to the following groups:Sham: hyperglycemia and surgery without MCAO.Non-stroke group: hyperglycemia without MCAO.Normoglycemic group: normoglycemia with MCAO.Non-treated hyperglycemic group: hyperglycemia with MCAO.Intravenously treated hyperglycemic group: Hyperglycemia with MCAO and intravenous insulin administration (dosage, 3 U/day).Subcutaneously treated hyperglycemic group: Hyperglycemia with MCAO and subcutaneous insulin administration (dosage, 3 U/day).

##### Randomization

We will follow RIGOR recommendations for animal research in terms of randomization and blinded study [20]. Each rat will be sequentially assigned to a study group based on the randomization plan. To maintain the blinding during the course of the study, we will ensure that the researcher who evaluates the endpoints and performs the laboratory analyses will not have access to the randomization codes, and a different researcher will perform the surgery, hyperglycemia induction and insulin administration. Following the STAIR recommendations, both female and male rats will be included (1:1 ratio) [21]. The stage of estrous cycle will be recorded. If variability is observed in the final results, a specific post-hoc analysis of the estrous cycle stage will be performed.

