##### Sample size estimates

Based on data from previous studies [11, 25] and using the statistical software NCSS PASS 11 (NCSS, Utah, USA), we calculated that a sample of 10 rats per group will be required to achieve a power of 80% (1-beta) and a level of significance of 5% (alpha) to detect a significant effect of GV on the study endpoints.

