### Statistical analysis

The statistical analysis will be performed with advice from the Department of Biostatistics of La Paz University Hospital. ﻿For the continuous variables, the following information will be provided: number of participants, mean, standard deviation, median, minimums, maximums and 25% and 75% quartiles. For the categorical variables, the frequency distribution and 95% confidence interval (CI), if applicable, will be provided. The analysis of the prognostic influence of GV on stroke outcomes will be performed in an exploratory manner without assumptions. We will first analyze GV as a continuous variable, comparing it with primary and secondary endpoints using Student’s t-test or the Mann–Whitney U test, as appropriate. We will also compare GV according to the various insulin types and administration routes applied to the patients according to the physician’s discretion. The comparisons will be performed with the one-way analysis of variance test. Secondly, we will perform a step forward logistic regression analysis for the endpoints that achieved a difference with a *P* value < 0.1 in the mean comparison tests, adjusting for age and baseline National Institutes of Health Stroke Scale score. The results will be expressed as odds ratios (OR) with 95% CI. In case of lack of homogeneity in the variances, we will use non-parametric tests (Kruskal–Wallis and Mann–Whitney test).

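### Rats are included 1:1 by sex, but no named analysis carries sex; adding it is a cheap gain in precision for the animal comparisons

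*Protocol article*

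**What the plan says.** - **Sex ratio.** The animal Randomization section says "both female and male rats will be included (1:1 ratio"). It does not say whether the ratio holds within each group or only overall.
- **Allocation.** Study groups: "A total of 60 Sprague–Dawley rats (8–9 weeks old, weighing 200–250 g) will be randomly assigned to the following groups". Randomization: "Each rat will be sequentially assigned to a study group based on the randomization plan". Neither mentions stratifying by sex.
- **Sample size.** The animal Sample size estimates section says "a sample of 10 rats per group will be required to achieve a power of 80% (1-beta"), at "a level of significance of 5% (alpha"). It gives no effect size and no SD.
- **Primary animal question.** Under the animal Primary endpoint, the question is whether the insulin route, intravenous or subcutaneous, affects GV. That contrast has 10 rats per side.
- **Analysis.** The Statistical analysis section follows both studies and is the only one. It names the t-test or Mann-Whitney test, one-way ANOVA ("The comparisons will be performed with the one-way analysis of variance test"), and Kruskal-Wallis or Mann-Whitney when variances differ. The only adjustment is for age and baseline NIHSS, in the logistic regression.
- **Sex-linked analysis in rats.** "If variability is observed in the final results, a specific post-hoc analysis of the estrous cycle stage will be performed".

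**The concern.** The plan fixes sex by design and then has no stated use for it in the analysis. With both sexes mixed in each group and a single-factor test, a male-female difference in GV is counted as noise between animals. With 10 rats per side there is little precision to spare.

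The plan does foresee sex-linked variation, but its answer is the estrous-stage analysis. That analysis is confined to females (about 5 per group if the ratio holds within groups, split further by stage), and an undefined look at the results sets it off. It can neither estimate nor remove a male-female difference.

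At stake is the power of the route contrast and of the other animal comparisons. The validity of the comparison is not in question.

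**Working it through.** **Inputs.** From the documents: 10 rats per group, 80% power, alpha 5%. Assumed: a two-sided test; the 80% applied to a two-group comparison of means; and the sex difference s, in units of the within-sex SD, which the documents do not give (0.5 to 1.5 is shown).

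**Step 1: the plan's own figure.** Ten per group cannot be reproduced without an effect size or SD. It can only be solved backwards:
- normal approximation: d = (1.960 + 0.842) × √(2/10) = 1.253;
- noncentral t, 18 df: d = 1.325.

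**Step 2: error variance with sex left out.** In a 1:1 mix each animal's mean lies s/2 above or below the centre, which adds s²/4 to the variance. The SD is multiplied by √(1 + s²/4):
- s = 0.5: √1.0625 = 1.031;
- s = 1.0: √1.25 = 1.118;
- s = 1.5: √1.5625 = 1.250.

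**Step 3: power if d = 1.325 is on the within-sex scale.** The formula divides d by the Step 2 factor (18 df). The simulation uses exactly 5 females and 5 males per group (100,000 runs). The model with sex keeps d = 1.325 on 17 df.

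| s | Sex omitted, formula | Sex omitted, simulated 5 + 5 | Sex in model, 5 + 5 |
|---|---|---|---|
| 0.5 | 77.6% | 78.2% | 79.7% |
| 1.0 | 70.8% | 72.2% | 79.7% |
| 1.5 | 61.1% | 61.8% | 79.7% |

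If sex has no effect, the comparison is 80.0% against 79.7%. The lost degree of freedom costs about 0.3 points.

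**Step 4: power if the planning SD already mixed the sexes.** Unadjusted power is then the planned 80%. Adjusting multiplies d by the Step 2 factor (17 df, 5 + 5 per group), which gives 82% at s = 0.5, 88% at 1.0 and 94% at 1.5.

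**Step 5: type I error of the unadjusted t-test.** With exact 5 + 5 balance the simulated rate is 4.3% at s = 0.5, 2.8% at 1.0 and 1.4% at 1.5. With 30 females and 30 males randomized without stratification it is about 5% at each of these values.

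**Step 6: adjusting without stratifying.** Chance imbalance in sex makes adjustment dearer. In a simulation with unstratified allocation, the model with sex has about 77 to 78% power whatever s is. The unadjusted test has about 80% at s = 0, 78% at 0.5, 71% at 1.0 and 61% at 1.5. So if sex has no effect the cost is 2 to 3 points, and at s = 0.5 the two are level. This is why stratification belongs in the fix.

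**The case against.** The strongest case on the other side has four parts.

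1. **No test is assigned to the rats.** The ANOVA sentence follows directly on one about insulin given to patients, and the t-test sentence concerns stroke outcomes. A one-way rat analysis is inferred from the shared section, and a fuller protocol or SAP may include sex. This stands, and the point is therefore conditional. Even so, every group comparison named is single-factor, and the article does commit itself on sex-linked variation in rats through the estrous-stage rule.
2. **The 80% power may not be lost.** A reader might infer that the stated power is not reached. The documents do not support that: the planning SD is not shown, and if it came from mixed-sex animals nothing is lost against plan. The power statement is also worded for an effect of GV on the study endpoints, not for the route contrast on GV.
3. **The test may not be conservative.** A reader might infer that the true type I error lies below 5%. That needs exact balance within groups, which the article does not state. Without stratification the rate stays at about 5%.
4. **The estrous-stage analysis is openly called post hoc, and stage is recorded regardless.** This stands. Nothing is hidden and no confirmatory claim rests on it. What remains is that its trigger is undefined and that it does not address the male-female difference.

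An unadjusted comparison of randomized groups is valid and unbiased, which also stands.

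**Conclusion.** The point holds as an efficiency improvement. Sex is a 1:1 factor in the animal design, no named analysis contains it, and the estrous-stage rule does not fill the gap. If the named tests are used for the rats, the price depends on a sex difference that the documents do not give. On a within-sex planning scale the loss is about 2 points of power at 0.5 SD, about 8 at 1.0 SD and about 18 at 1.5 SD (80% less the simulated 78.2%, 72.2% and 61.8%). It is therefore small up to 0.5 SD and material from about 1 SD. On a mixed-sex planning scale there is no loss against plan, but a gain of about 2 to 8 points at 0.5 to 1.0 SD is forgone. The result is not biased, and no figure in the article is shown to be wrong.

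**What to change.** - State that the rat randomization is stratified by sex, with 5 females and 5 males in each of the six groups.
- Analyse GV and the other animal endpoints by a linear model with group and sex, and report the intravenous-subcutaneous contrast from that model.
- Report estrous stage descriptively in all females, and drop the condition that variability be observed first.

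The cost is a few sentences, one residual degree of freedom and no extra animals. If allocation has already been made without stratification, the adjusted model is still valid, at the higher price given in Step 6 of the working.

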##### Intervention

Hyperglycemia will be induced by an intraperitoneal injection of nicotinamide (210 mg/kg) (EMD Millipore, Germany). Fifteen minutes later, an intraperitoneal injection of streptozotocin (60 mg/kg) (EMD Millipore, Germany) will be administered [22, 23]. Blood glucose levels will then be measured using a glucometer (ACCU-CHEK, Performa, Germany) for 72 h. The animals with a blood glucose level > 250 mg/dL will be considered hyperglycemic [23].

To induce a stroke, the rats will be anesthetized via an intraperitoneal injection of a solution of ketamine (25 mg/kg) and diazepam (2 mg/kg). Analgesia will be induced with a subcutaneous injection of meloxicam (2 mg/kg). To perform the MCAO, a small craniotomy will be performed, and the right middle cerebral artery will be permanently ligated just before its bifurcation. Both common carotid arteries will then be occluded for 60 min, as previously described [24]. A device for CGM will then be implanted subcutaneously for at least 96 h.

Insulin treatment will be administered 4 h after MCAO and until 96 h later. The administration will be intravenous or subcutaneous, depending on the experimental group. The dosage per animal (3 U/day) has been determined based on the results of a previous dose–response study [23].

##### Study schedule

The study will last a total of 31 days for each rat, according to the schedule illustrated in Fig. 1.

**Fig. 1 Fig1:**
[figure not shown]
Experimental animal protocol. Hyperglycemia will be induced 72 h before surgery. The rats will then undergo a IS through permanent middle cerebral artery occlusion or sham surgery. Insulin treatment will be intravenously or subcutaneously administered 4 h after IS induction and up to 96 h later, after which the blood glucose levels will be continuously monitored. A functional evaluation will be performed at 24 h, 1 week and 4 weeks post-stroke. Peripheral blood will be extracted 24 h, 72 h and 4 weeks after the stroke. The MRI will be analyzed at 24 h and 4 weeks post-stroke. Four weeks after the stroke, the animals will be euthanized, and histological analyses will be performed

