##### Primary endpoint

GV, defined as the standard deviation of the mean glucose level [17]. We will analyze whether the insulin administration route (intravenous and subcutaneous) affects the GV.

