##### Secondary endpoints

Functional evaluation, analyzed by a researcher blinded to the experimental groups, at 24 h, 1 week and 4 weeks post-stroke. Motor and sensory performance will be evaluated using a variant of Rogers’ functional scale [23]. The beam walking test will evaluate hindlimb functions by testing the rats’ ability to traverse a wooden beam [23].Lesion size will be analyzed at 24 h and 4 weeks post-stroke by 7-T horizontal bore magnetic resonance imaging (MRI) (Bruker PharmaScan, Ettlingen, Germany), using T2-weighted (T2-W) spin-echo anatomical images, by a researcher who will be blinded to the experimental groups.Brain damage and repair-related markers will be analyzed at 4 weeks. The perilesional area of the brain will be studied in detail using immunofluorescence for superoxide dismutase 2, catalase, vascular endothelial growth factor (VEGF), brain-derived neurotrophic factor (BDNF), synaptophysin, glial fibrillary acidic protein, myelin basic protein and oligodendrocyte. Immunofluorescence images will be acquired by a researcher (who will be blinded to the experimental groups) using a Leica TCS-SPE confocal microscope (Leica Microsystems, Heidelberg, Germany). Plasma levels of damage and repair markers will be studied using Multiplex (eBioscience) and by ELISA (System Biosciences, Mountain View, CA, USA). The following markers will be analyzed: interleukin-1, interleukin-6, interleukin-10, vascular cell adhesion molecule, tumor necrosis factor alpha, matrix metalloproteinase 9, VEGF, BDNF, anti-Nogo A.

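### The rat study gives two incompatible times for continuous glucose recording, so its primary endpoint may not cover the insulin period; if recording starts at surgery, the 24 h MRI falls inside it

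*Protocol article*

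**What the plan says.** All references are to the protocol article.

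- **Animal study, Primary endpoint.** GV is the SD of glucose, and the question is comparative: "We will analyze whether the insulin administration route (intravenous and subcutaneous) affects the GV". No time window is given for the rats.
- **Animal study, Intervention.** After the occlusion procedure, "A device for CGM will then be implanted subcutaneously for at least 96 h". On insulin: "Insulin treatment will be administered 4 h after MCAO and until 96 h later".
- **Fig. 1 caption.** Insulin is given from 4 h after stroke induction "up to 96 h later, after which the blood glucose levels will be continuously monitored". The Study schedule section refers the reader to Fig. 1 for the schedule.
- **MRI in rats.** The caption states "The MRI will be analyzed at 24 h and 4 weeks post-stroke". Secondary endpoints gives the same two times for lesion size, at 7 T.
- **Patient study.** Patients wear a subcutaneous CGM for 96 h (clinical Intervention section). Table 1 excludes those with "Predicted need for an MRI within the first 96 h after inclusion".

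**The concern.** The route comparison is informative only if glucose is recorded during treatment. One text provides for that. The other, taken at its word, places continuous recording after treatment, when GV could not show what the two routes do while insulin is being given. Glucose that was not recorded during insulin cannot be recovered later.

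The second issue depends on the first. If recording starts at surgery, the 24 h scan falls within the minimum sensor period. If the sensor has to come off, or reads unreliably in the scanner, part of the primary-endpoint record is lost. Unless that loss is handled in the same way in every group, the GV values are not strictly comparable.

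**Working it through.** **Check of the stated timeline.** Hyperglycemia is induced 72 h before surgery (3 days) and the rats are followed for 4 weeks (28 days). 3 + 28 = 31 days, which matches the stated duration per rat. The frame is consistent; the conflict lies inside it.

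**Windows, in hours after occlusion.**

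- Insulin starts at 4 h. Its end is ambiguous: 96 h if counted from the occlusion, 100 h if counted from the first dose. The insulin period is therefore 4 to 96 (92 h) or 4 to 100 (96 h).
- CGM under the Intervention section: from about 0 to at least 96 h.
- CGM under the literal caption: from the end of insulin, 96 or 100 h.

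**Insulin time covered by guaranteed CGM.** Overlap = max(0, min(both ends) − max(both starts)).

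| Text that governs | Insulin 4–96 h | Insulin 4–100 h | 24 h MRI inside CGM period? |
|---|---|---|---|
| Intervention (CGM 0–96) | 96 − 4 = 92 of 92 h | 96 − 4 = 92 of 96 h | Yes |
| Caption, literal | 0 of 92 h | 0 of 96 h | No |

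The Intervention section also describes 60 min of carotid occlusion before the sensor goes in. Starting CGM at 1 h and running it to 97 h gives 92 of 92 h or 97 − 4 = 93 of 96 h, so the picture does not change.

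The last column matters: the two problems belong to alternative readings. Under the caption, recording misses insulin but the scan does not touch it. Under the Intervention section, recording suits the endpoint but the scan falls within it.

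**Worst case for the scan (assumption: sensor removed at 24 h and not replaced).** CGM kept: 24/96 = 25%. Insulin time kept: 24 − 4 = 20 h, which is 20/92 = 22% or 20/96 = 21%. If the sensor were replaced after the scan, the loss would be only the gap.

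**Is a conflict between MRI and CGM documented?** The patient study keeps anticipated MRI out of the 96 h for which patients wear the sensor. No reason is given, the rat device is not named, and the statement that one brand is used applies to the study centers. The inference is reasonable but it remains an inference.

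**The case against.** The strongest reply is that the caption is merely loose. The Intervention section is explicit and fits the stated aim, whereas the literal caption would defeat that aim and is an unlikely plan. The phrase may have been meant to refer back to stroke induction or to the first dose. The figure itself is not available here and might settle it. This stands as a reason to expect an easy correction. It does not remove the contradiction, because the article names Fig. 1 as the schedule and no other text resolves it.

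Three stronger readings are tempting, and the documents do not support them.

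- *The MRI will break the record in every rat.* No section says that the rat sensor is incompatible with 7 T or must be removed, and a condensed article may leave sensor handling to the full protocol. The scan times are also given as post-stroke, and two of the six groups have no occlusion. A gap common to both insulin groups need not bias the route comparison.
- *The record is both mistimed and interrupted.* These are alternatives, as the table shows.
- *The 4 h before insulin inflates the primary result.* If glucose fell at once from 300 to 150–200 mg/dL (assumed values), the step would contribute √((4/96)(92/96)) × D = 0.1998 × D to the SD, which is 20–30 mg/dL for D = 100–150, added in quadrature. Both insulin groups start at 4 h with the same daily dose, so both carry this lead-in. It bears mainly on treated versus untreated comparisons and would affect the route comparison only if the fall differed by route. It is not a measure of harm to the primary question.

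The missing GV window for rats is not a fault in itself, since an analysis plan could supply it. It matters here because the window cannot be inferred while the start of recording is contradictory.

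**Conclusion.** The contradiction is real and concerns when the rat study's primary endpoint is measured. Guaranteed coverage of insulin time is 92 of 92 h or 92 of 96 h under one text and 0 h under the other. This rests on reading the caption literally, and on no other text or visible figure overriding it.

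The MRI overlap is conditional. It arises only if the Intervention section governs, and it costs data only if the sensor cannot stay in place or be trusted during the scan. The 21–25% retention figures are a worst case under an assumption that the documents do not make.

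A reader might infer that the rat GV endpoint is certain to be invalid, or that the patient mortality analysis is affected. Neither follows: the first depends on which text governs, and the second study is separate. The point is worth correcting before animals are run.

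**What to change.** 1. Reconcile the animal Intervention section and the Fig. 1 caption so that CGM recording covers the whole insulin period. In the same edit, state whether insulin ends 96 h or 100 h after occlusion, and check that the minimum CGM duration reaches that point. Which end time was intended is for the investigators to say.
2. State in the Primary endpoint section that GV is computed over one common window, matched to the insulin period and identical in all six groups. For rats without occlusion, define a matched time zero (surgery or its equivalent).
3. Keep the 24 h MRI, which serves a stated secondary endpoint. State what happens to the sensor at the scan. If it must be removed or its readings are unreliable, exclude the same pre-set interval from GV in every group, whether or not a given rat is scanned.

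The cost is a few sentences and, if the sensor is affected, a gap of a few hours in the CGM record. Moving the first scan until after sensor removal would avoid the gap but would give up the 24 h lesion size, and the evidence here does not justify that trade. A common window does not remove the fall in glucose after insulin starts, so treated versus untreated comparisons of GV should be read with that in mind.
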